## Methods/Design

A field trial with one intervention and one comparison group, with ex ante and ex post measurements will be conducted in two IMSS primary care clinics in Mexico City. The clinics will be selected for convenience; each clinic must have more than 20 family doctors' offices and available space for the intervention (consulting room and an area for group counseling) and should have accepted to participate in the study; The intervention will be conducted in one clinic and the other clinic will serve as a comparison group, where the usual care for climacteric stage women will be observed.

The study population will consist of women affiliated with IMSS, between 45 and 59 years of age with a maximum of 5 years after menopause. The women should be users of the clinic, and should not have mental conditions that would prevent them from understanding the information or from taking independent decisions (dementia, mental retardation or psychosis), a physical disability that would impede them from participating (hearing loss, diseases affecting physical mobility as severe forms of rheumatoid arthritis), medical diagnosis of depression, diabetes mellitus, hypertension, renal or liver failure, and/or cancer, because patients with these diseases require specific care provided by several specialists. All women must agree to participate in the study through written informed consent.

The project was authorized by the National Research and Ethics Committee of the IMSS.

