### Data collection

Information on the study variables will be collected on three occasions: when the woman enters to the study (baseline), once intervention is complete (at three months) and after three more months of follow-up (six months).

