### Sample size

The sample size for the primary outcome (HR-QoL) was estimated by using the formula to test change in the mean of two normally distributed samples in longitudinal studies [50]. An average increase of at least 10 points in one or more domains of WHQ23 in the intervention group compared with control group women was considered to be clinically relevant. The assumptions included: a mean HR-QoL score of 64.9 points (standard deviation of 23.4 points) in the domain of general well-being [51], α = 0.05 (for one-sided hypothesis) and β = 0.20. The number of women by group, assuming a drop-out rate of 20% will be 107.

We also estimated a sample size for regular leisure time physical activity considering that this is the outcome variable more difficult to achieve. It was assumed that only 17% of women in Mexico engaged in some type of regular leisure time physical activity [11] and a positive increase of at least 10% will be achieved after women participation in the IHCM. For this calculation, we used the formula to test the difference of proportions between two populations [50] with a = 0.05 (one side) and the power of 80%. The total number of women by group to include assuming a drop-out rate of 20% will be 207.

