### Statistical analysis

The women characteristics of each intervention and comparison groups will be compared by using the Chi-square test to ascertain whether the groups were equivalent.

The effects of intervention for categorical outcome variables (regular leisure time physical activity, healthy diet) will be measured by comparing the baseline and post-intervention evaluation stages for differences in these variables using Chi-square test. Absolute percentage differences and corresponding 95% confidence intervals will be calculated.

Scores for the HR-QoL on the WHQ23 scale, the self-efficacy on the PHS-ES scale, the empowerment on the short form scale, knowledge about the climacteric stage, and menopause and self-care-related activities will be calculated according to the scoring algorithms. Measures of central tendency and distribution will be examined for these variables at the different measurement periods. The differences in the baseline and post-intervention stages for outcome variables will be compared within each group, and differences between the groups will be compared using the differences-in-differences (D-in-D) estimator [52]. The generalized linear model (GLM) will be used to assess changes in the main outcome variable controlling for baseline measures and other study variables as covariates. The GLM methods allow for modeling the correlation of the repeated observations on the same subjects [53].

The p value <0.05 will be considered as statistically significant. The analysis will be performed with the Stata 11.0 statistical software (Stata 11.0, Stata Corp; College Station, TX).

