## Discussion

In primary care services, it is essential to provide a source of care that has continuity and coordination, and comprehensively covers the health needs of people. The constraints resulting from limited resources and restrictive organizational characteristics of institutionalized healthcare allows a limited range of changes, and these circumstances promote that innovative healthcare models should be carefully designed and evaluated to demonstrate healthcare service relevance and feasibility. Relevance, in this case, refers to meeting the health needs of climacteric stage women and to demonstrating its potential benefit. Feasibility means that the new model of care is applicable in the local context. An integrative health care model (bio-psycho-social, multidisciplinary and women-centered) with the empowerment approach may be a better alternative to ensure that women engage in their self-care and understand its importance to their present and future health and quality of life. The evaluation of the effectiveness of this research-based model can guide the feasibility of extending it into an operational model through a specific program.

The possible limitations of the study may include the following:

It was decided to perform the intervention in one clinic, taking another as a control to prevent women from both groups from communicating and transmitting information between them. However, the implementation of the study in two clinics may result in difference baseline characteristics of women in both groups. To overcome this limitation in the data analysis step, the regression methods will be used to adjust the results of the study for possible differences between groups.

Furthermore, the baseline evaluation can affect women in the control group resulting in them seeking counseling regarding the climacteric stage, attending screening programs, and changing their lifestyles.

The request for voluntary collaboration of family doctors and women could result in better doctors and women with healthier lifestyles agreeing to participate. Previous studies have reported that patients with unhealthy lifestyles are usually reluctant to participate. To confirm or disregard this limitation we will apply a short list of questions about the general characteristics and lifestyles to women who do not agree to participate in the study.

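### For physical activity and healthy diet, the plan states the intervention effect as a baseline-to-post Chi-square, which ignores pairing and does not name the between-clinic contrast

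*Protocol article*

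**What the plan says.** All references are to the protocol article.

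- **Design (Methods/Design).** "A field trial with one intervention and one comparison group, with ex ante and ex post measurements". There is one clinic per group, chosen for convenience.
- **Measurement (Data collection).** Each woman is assessed "when the woman enters to the study (baseline), once intervention is complete (at three months) and after three more months of follow-up (six months"), so baseline and later values come from the same women.
- **Effect for the binary outcomes (Statistical analysis, second paragraph).** Two outcomes are named here, physical activity and diet, and the plan says of the effect on them that it "will be measured by comparing the baseline and post-intervention evaluation stages for differences in these variables using Chi-square test". Absolute percentage differences with 95% confidence intervals follow. The paragraph mentions neither the comparison clinic nor a paired method.
- **Effect for the scores (Statistical analysis, third paragraph).** The paragraph opens with the questionnaire scores. It then says that baseline-to-post differences in outcome variables are compared within each group, and "differences between the groups will be compared using the differences-in-differences (D-in-D) estimator". The model said to handle repeated observations is narrower: "The generalized linear model (GLM) will be used to assess changes in the main outcome variable".
- **Sizing of physical activity (Sample size).** "we used the formula to test the difference of proportions between two populations", with 17% at baseline, an increase of 10%, one-sided 0.05, 80% power and 20% drop-out, giving 207 per group.
- **Limitations (Discussion).** "the baseline evaluation can affect women in the control group resulting in them seeking counseling", attending screening and changing lifestyle. Regression will also be used to adjust the results for differences between groups; no outcome is named.

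**The concern.** Two things are at stake.

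1. **The variance.** An ordinary Chi-square for two proportions treats baseline and follow-up as separate samples. With repeated measurements its variance leaves out the within-woman covariance, and so does any interval built the same way.
2. **The contrast.** The sample size concerns a difference between clinics, whereas the sentence defining the effect concerns a difference between times. Change that would have happened anyway, such as a reaction to the baseline interview or a seasonal or general trend, is part of a before-after difference and would be credited to the care model. Without randomisation, the comparison clinic is the plan's main protection against that.

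Both outcomes are secondary, but physical activity carries the larger of the two sample sizes (207 against 107 per group).

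**Working it through.** **Inputs.** From Sample size: 17% at baseline, 27% after (the 10% increase read as percentage points), 207 per group, 20% drop-out. Completers: 207 × 0.8 = 165.6, taken as 165 in the formulas and 166 in the power simulation. Tests are two-sided at 0.05. The article gives no within-woman correlation r and no shared change between clinics; both are assumptions, shown as ranges.

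**The plan's own figure.** The two-proportion formula gives n = [1.645·√(2 × 0.22 × 0.78) + 0.842·√(0.17 × 0.83 + 0.27 × 0.73)]² / 0.10² = 212 per group before drop-out, and 212 / 0.8 = 265 after. The stated 207 is not reproduced once drop-out is included. That is a separate matter; 207 is taken as given here. The formula itself confirms that the sized quantity is a between-group difference.

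**Step 1: pairing ignored, no change anywhere.** The true variance of the before-after difference is (1 − r) times the one the unpaired test uses. The actual rejection rate is therefore 2·[1 − Φ(1.96/√(1 − r))].

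| r | 1.96/√(1 − r) | Unpaired Chi-square, formula | Chi-square, simulated | McNemar, simulated |
|---|---|---|---|---|
| 0 | 1.96 | 5.0% | 5.2% | 5.1% |
| 0.3 | 2.34 | 1.9% | 1.8% | 4.9% |
| 0.5 | 2.77 | 0.6% | 0.65% | 5.3% |
| 0.7 | 3.58 | 0.03% | 0.05% | 4.8% |

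(20,000 simulated trials, 165 women.) An unpaired interval is too wide by the factor 1/√(1 − r): 1.20, 1.41 and 1.83 for r = 0.3, 0.5 and 0.7.

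**Step 2: equal rise in both clinics, no intervention effect.** Let p = 0.17 and q = p + rise, with m their mean.

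- Standard error used by the test: s₀ = √(2m(1 − m)/165)
- True standard error: s = √([p(1 − p) + q(1 − q) − 2r√(p(1 − p)q(1 − q))]/165)
- Probability of a significant increase: 1 − Φ((1.96·s₀ − rise)/s). The opposite tail is added, but is negligible once there is a clear rise.

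Example, 8 points, r = 0.5: s₀ = √(2 × 0.21 × 0.79/165) = 0.0448; s = √((0.1411 + 0.1875 − 0.1627)/165) = 0.0317; (0.0879 − 0.08)/0.0317 = 0.25; probability 40%.

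| Shared rise | r = 0 | r = 0.3 | r = 0.5 | r = 0.7 |
|---|---|---|---|---|
| 3 points | 11% | 7% | 4% | 1% |
| 5 points | 21% | 17% | 12.5% | 7% |
| 8 points | 43% | 42% | 40% | 37% |
| 10 points | 59% | 61% | 63% | 66% |

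In simulation with the 8-point shared rise, the between-group difference-in-differences stays at 5%, because the rise is the same in both clinics.

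**Step 3: power for 17% to 27% in the intervention clinic, comparison clinic flat, r = 0.5, 166 per group (simulated).** Unpaired before-after Chi-square 64%; McNemar 89%; difference-in-differences about 64%. By formula with 165 per group, two-sided power of the difference-in-differences is 37%, 49%, 63% and 84% at r = 0, 0.3, 0.5 and 0.7.

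**The case against.** The strongest reply is that the comparison clinic is not left out. The difference-in-differences sentence speaks of outcome variables without limiting them to scores, and Study variables lists physical activity and diet among the outcomes. The very next sentence narrows the GLM to the main outcome, so the authors restricted scope when they meant to. The two-group design, the between-population sizing and the general promise of regression adjustment all point to a between-group effect. The Discussion also lists lifestyle change among controls as a limitation, which makes most sense if controls enter the estimate. This stands as far as it goes: a reader might infer that the plan excludes the comparison clinic for these outcomes, and the text does not support that.

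It does not settle the point. The binary outcomes have their own paragraph with its own statement of the effect, and the between-group sentence comes in a paragraph introduced by the scores. On the generous reading there are still two competing definitions of the effect, and the unpaired test remains.

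It could also be said that McNemar's statistic is itself a chi-square. But the same section uses the same name for comparing characteristics between the two groups, so the ordinary test is the natural reading.

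Three further limits are accepted. The pairing error creates no false positives under positive correlation. The Discussion says only that control women can be affected, so it does not predict a rise of any size. And the false-positive rates depend heavily on the assumed rise: for 3 points they are 1–11%.

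**Conclusion.** The point holds in limited form. The test named for physical activity and healthy diet does not suit repeated measurements of the same women. If within-woman correlation is positive it is too cautious: null rejection is about 2% to below 0.1% for correlations of 0.3 to 0.7, with intervals too wide.

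The more serious weakness is that the sentence defining the effect does not name the between-clinic contrast. An analyst could follow it to the letter and report a before-after change as the intervention effect. If both clinics moved equally with no true effect, that report would be wrong in roughly 7–21% of trials for a 5-point rise, about 40% for 8 points and 59–66% for 10 points. These figures rest on assumed correlations of 0 to 0.7 and an assumed shared rise; the article gives neither. They measure the risk of one permitted reading and do not show that the authors intend it. The primary outcome is not affected, since difference-in-differences and a repeated-measures model are named for it.

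**What to change.** In Statistical analysis:

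1. State that the effect for physical activity and healthy diet is the group-by-time contrast, that is, the difference between clinics in the change in percentage. Estimate it by a binomial GEE clustered on woman, adjusted for covariates, with a 95% confidence interval.
2. Replace the Chi-square for within-group change by McNemar with a paired confidence interval, and label that result descriptive.

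This changes wording only and needs no new data. It costs apparent power: about 64% for the between-group contrast against 89% for a paired before-after test (two-sided, assumed correlation 0.5, 166 completers per group). The contrast also removes only change common to both clinics. With one clinic per group, change specific to either clinic stays mixed with the intervention effect, and the report should say so.

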**Figure 1 F1:**
[figure not shown]
**Conceptual model of integrative health care for climacteric stage women**.

The characteristics of population, structure and processes of care within social security allows the implementation and testing of an integrative health care model (IHCM) for climacteric stage women (Table 1). The lessons learned from this first intervention that will be implemented in social security settings will provide further elements and evidence to eventually propose a study aimed at the population with social security in other developing countries. This work aims to develop an IHCM applicable in primary care services (family medicine clinics) for climacteric stage women. The effectiveness of the model will be evaluated through the following aspects: a) improved HR-QoL; b-d) increased empowerment, self-efficacy and knowledge regarding climacteric stage, and health-related self-care activities; e) increased use of screening services for breast cancer, cervical cancer, diabetes and hypertension; f-g) improved lifestyles: regular leisure time physical activity and healthy diet.

**Table 1 T1:** Structure and population characteristics of health institutions in Mexico

	Mexican Institute of Social Security	Ministry of Health
Population	Formal sector workers and their families	People without formal employment contracts, or unemployed and the rural population
Organization	Centralize	Decentralize
Drug acquisition, laboratory and screening tests	Covered by the social insurance	Covered partially by the insurance + out of pocket payments
Medical doctors	1.4 per 1000 habitants	1.3 per 1000 habitants
Nurses	2.0 per 1000 habitants	1.7 per 1000 habitants

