### Study variables

The main outcome variables will be:

Health-related quality of life (HR-QoL), which will be measured with the revised version of Women's Health Questionnaire (WHQ23) [43]. This is a specific questionnaire for women in perimenopause, menopause and post menopause stages, that comprises six domains: anxiety/depression, well-being, somatic symptoms, memory/concentration, vasomotor symptoms and sleep problems. The WHQ23 also has two optional domains: sexual behavior and menstrual symptoms, which will apply only to women who are sexually active or who have menstrual periods. The highest value for each domain score is 100, which means high HR-QoL, and the lowest is 0, which means low HR-QoL.

Other outcome variables will be:

1) Empowerment of women in relation to their self-care measured by the empowerment scale, which was modified from the diabetes empowerment short scale [44] to be used in climacteric women. The maximum score of empowerment is 5, the minimum is 1.

2) Self-efficacy of women in relation to menopause and its care will be assessed with Perimenopausal Health Self-efficacy Scale (PHS-ES) which consists of 23 items [45]. The maximum score of PHS-ES is 207 (high self-efficacy) and the minimum is 23 (low self-efficacy).

3) Women's knowledge about the climacteric stage will be estimated with a questionnaire developed *ex profeso*. The questionnaire consists of 24 items that assess the following aspects: what is the climacteric stage, what are climacteric symptoms and health risks, and how can they be prevented during the climacteric stage. The minimum score on the scale corresponds to -24 points (without knowledge) and the maximum 24 points (full knowledge).

4) The use of screening services for: a) breast cancer by mammography in the last two years; b) cervical cancer by Pap-test in the last three years in women without a history of total hysterectomy; c) diabetes by measuring fasting plasma glucose in the last three years; d) hypertension: by measuring the systolic and diastolic blood pressure in the last year. The use of screening services will be estimated as the sum of the number of screening services that women used, divided by the total number of screening services recommended according to IMSS regulations and multiplied by 100.

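### Regression adjustment for clinic differences is promised for the study's results, but the analysis section specifies covariates only for HR-QoL, one of seven effectiveness outcomes

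*Protocol article*

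**What the plan says.** **Design.** In the Methods/Design section, "The clinics will be selected for convenience", and "The intervention will be conducted in one clinic and the other clinic will serve as a comparison group". There is no randomisation.

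**Remedy claimed.** The limitations part of the Discussion accepts that using two clinics may produce groups with different baseline characteristics. Its answer is that "the regression methods will be used to adjust the results of the study for possible differences between groups". The sentence is not restricted to any one outcome.

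**Model specified.** The Statistical analysis section names a single covariate-adjusted model, the generalised linear model (GLM), which "will be used to assess changes in the main outcome variable controlling for baseline measures" and for further study variables. Under Study variables, HR-QoL is the only entry in the main group, and the Sample size section calls it the primary outcome. The remaining six follow under the line "Other outcome variables will be": empowerment, self-efficacy, knowledge, screening use, physical activity and diet. All seven are named as effectiveness aspects in the study objectives, including "increased use of screening services for breast cancer, cervical cancer, diabetes and hypertension".

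**The concern.** The Discussion offers regression as the protection against the main weakness of the design. The analysis section assigns a method to each type of outcome and attaches that protection to one of them. An analyst who followed the analysis section as written would not deliver what the Discussion tells readers to rely on.

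What is at stake is how most of the results are read. If the women at one clinic have more schooling, or differ in age or employment, they may learn more or change their habits more over six months under either model of care. Without adjustment, part of that difference could be credited to the integrative model. The point matters most for physical activity, which has its own sample-size calculation, and for diet. Both are self-reported, and the Discussion already warns that their effects may be overestimated.

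**Working it through.** The question turns on wording, so the check sets the stated method for each outcome beside the Discussion's promise.

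| Effectiveness outcome | Method in the Statistical analysis section | Covariates named? | Between-clinic contrast stated? |
|---|---|---|---|
| HR-QoL | D-in-D, and GLM | Yes | Yes |
| Empowerment, self-efficacy, knowledge | Within-group change, then D-in-D | No | Yes |
| Physical activity, diet | Chi-square, baseline against post-intervention; absolute percentage difference with 95% CI | No | Not in that paragraph |
| Screening use | Not named; at most covered by the general reference to outcome variables in the D-in-D sentence | No | Only through that reference |

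Count: 1 + 3 + 2 + 1 = 7 outcomes. Covariate adjustment is stated for 1, which leaves 7 − 1 = 6.

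**What D-in-D does and does not remove.** Let the baseline means be L_I (intervention clinic) and L_C (comparison clinic), and let the shares of women with some characteristic, such as higher schooling, be s_I and s_C. Suppose the intervention has no effect, women without the characteristic change by m on average, and women with it change by m + δ.

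- Expected change, intervention clinic: (L_I + m + s_I·δ) − L_I = m + s_I·δ
- Expected change, comparison clinic: (L_C + m + s_C·δ) − L_C = m + s_C·δ
- D-in-D: (m + s_I·δ) − (m + s_C·δ) = (s_I − s_C)·δ

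The levels L_I and L_C cancel, so a stable clinic difference does no harm. The term (s_I − s_C)·δ remains. It is zero only if the clinics have the same mix or if the characteristic does not affect change. The document gives neither quantity.

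**What the before-after Chi-square does.** Applied within a clinic, it contrasts that clinic with itself over time, so the comparison clinic's change is never subtracted. The Discussion itself expects that the baseline interview may prompt comparison women to change their lifestyles. A before-after test in the intervention clinic cannot separate that kind of change from an effect of the model.

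**Weight of physical activity.** The Sample size section gives 107 women per group for HR-QoL and 207 for physical activity. The larger requirement therefore comes from an outcome with no stated adjustment.

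**The case against.** The strongest reply is that the two sections are compatible. The Discussion makes a general commitment to regression, the analysis section names the model for the main outcome, and nowhere is adjustment of the other outcomes excluded. D-in-D can itself be fitted with covariates. A condensed article may also leave the model for each secondary outcome to a fuller document.

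Part of this stands. The Discussion sentence can be read as covering all outcomes, so this is an inconsistency to reconcile and not a settled decision to leave six outcomes unadjusted. The argument from condensation is weaker. The article does not stay silent on the other outcomes: it assigns them methods, and those methods differ from the remedy claimed.

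A reader might infer that six outcomes will be compared raw between the clinics. The document does not support that. For the scores, D-in-D subtracts each group's own baseline. For physical activity and diet, the stated test is baseline against post-intervention, and no unadjusted between-clinic comparison is written down.

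A reader might also want to attach an inflated false-positive rate. Any such figure needs an assumed case-mix gap and an assumed effect of that gap, neither of which is given. For physical activity, a calculation based on follow-up rates alone would describe an analysis the plan does not state. A stable difference in activity between the clinics would already be present at baseline and would cancel from a contrast of changes.

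Finally, both clinics belong to the same institution and city and apply the same eligibility criteria, so case mix may turn out to be similar. That lowers the likely bias, but the plan itself treats imbalance as a real possibility.

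**Conclusion.** The inconsistency is real and worth correcting. The Discussion promises regression adjustment of the study's results, while the analysis section specifies it for one of seven effectiveness outcomes. The gap differs by outcome:

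- **Empowerment, self-efficacy, knowledge:** partial protection. Stable differences in level are removed; case-mix effects on change are not.
- **Physical activity and diet:** the widest gap. There is no covariate adjustment, and the paragraph that deals with them states no between-clinic contrast.
- **Screening use:** covered by general wording at best.

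No numerical size is attached, because the bias depends on the clinics' case mix and its effect on change, and the document gives neither. The conclusion rests on reading the main outcome variable as HR-QoL, which the Study variables and Sample size sections both support. It does not assume that the other outcomes would in fact go unadjusted.

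**What to change.** In the Statistical analysis section:

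1. Extend the repeated-measures GLM from the main outcome to all seven effectiveness outcomes, and name screening use among them. Include a group-by-time term and baseline covariates already collected, for example age, schooling, marital status and employment status.
2. Enter the covariates so that they can act on change. In a linear model with baseline and follow-up both as responses and complete data, constant covariate main effects leave the group-by-time estimate where it was. Conditioning on the baseline measure, as the HR-QoL model already does, or allowing covariate effects to vary with time would both work. The choice can be left to the analysis plan.
3. For physical activity and diet, replace the before-after Chi-square as the effect analysis with this adjusted between-clinic contrast of change. Keep the absolute percentage difference with its 95% confidence interval, from an identity link or by marginal standardisation after a logistic model.
4. Show the unadjusted D-in-D beside each adjusted estimate.

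In the Discussion, state that with one clinic per arm this controls measured patient case mix only and cannot remove a clinic-level effect. The minimum alternative is to restrict the regression claim there to HR-QoL, which makes the text consistent but leaves the other outcomes without the protection.

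The cost is revised wording and a few more models in the same software. No new data, visits or participants are needed.
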